#### Acceptability

The following indicators of acceptability including participant satisfaction, TSP counselor knowledge and attitudes, and the perceived effectiveness of the intervention in reducing depression will be evaluated using a 9-item questionnaire (67).

#### Fidelity

Fidelity will be assessed by asking supervisors to complete a semi-structured self-administered questionnaire to assess whether the interventions were delivered as planned.

Contextual influences will be assessed by asking TSP counselors to complete a semi-structured self-administered questionnaire to identify any facilitators or barriers to intervention delivery observed during group sessions. Additionally exit interviews with study participants will be conducted to assess participants’ knowledge, skills, or assets acquired during and after the interventions. This will provide insight into whether the interventions influenced targeted risk factors for depression.

### Determining cost-effectiveness

To assess the cost-effectiveness of providing TSP with SMHS vs. the provision of SMHS alone, we will adopt a societal perspective in our analysis. This approach encompasses not only the direct costs associated with the interventions—such as program delivery expenses—but also indirect costs like those stemming from the use of additional healthcare services and the loss of productive time due to participation in the interventions. We plan to devise a comprehensive questionnaire to gather detailed information on the utilization of supplementary healthcare resources, including visits to medical professionals covered by insurance, outpatient services, and expenditures on mental health medications, which may be influenced by the intervention.

The financial implications of implementing both the TSP & SMHS combination and the SMHS-only model will be meticulously calculated, focusing on contrasting these costs against the respective outcomes each model achieves, particularly regarding depression score improvements. It's crucial to clarify that the expense of conducting the research and any ancillary research activities, will be excluded from the cost-effectiveness evaluation.

Moreover, we intend to delve into the economic repercussions associated with time loss for different participant groups, including those volunteering without compensation, and the additional burden placed on individuals due to increased responsibilities linked to the study. To quantify these indirect costs, we will employ shadow pricing techniques. The identification of costs will be primarily based on project documentation and financial reports. For any costs not directly documented, we will turn to existing literature for estimates. Significant expenses related to services and procurements will be determined by the terms of reimbursement contracts or, in certain cases, prevailing market rates at the time of acquisition. Additionally, we will leverage databases such as the Uganda Bureau of Statistics (UBOS) to source pertinent data to inform our cost-effectiveness analysis, ensuring a robust and comprehensive evaluation of the interventions’ economic viability.

### Participant safety

During initial evaluations, participants will undergo thorough screening, and those for whom the interventions are considered medically unsuitable or hazardous will be excluded based on predefined criteria. Independent evaluators will monitor all participants for any adverse events at both 6- and 12-months post-intervention through a structured interview and report form. An adverse event (AE) encompasses any undesired or unintended sign, symptom, or medical occurrence linked to participation in tele-support psychotherapy, irrespective of its direct association with the therapy. Serious adverse events (SAEs) include any AE leading to outcomes such as death, a life-endangering situation, the necessity for hospital admission, or long-lasting or significant disability or incapacity. In this study, potential AEs might include suicide attempts resulting from an inadequate response to the tele-support psychotherapy sessions. A suicide management protocol is detailed in the study's risk management plan (see Supplementary File S2).

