In the trial phase, we shall conduct a pilot single-blinded randomized controlled trial to test the feasibility and

acceptability of using TSP in combination with standard mental health services(SMHS) vs. SMHS only to treat mild to moderate depression among youth in Kampala district. We aim to randomize 300 youth (1:1) to either both TSP and SMHS (*N* = 150) or SMHS only (*N* = 150). The 150 subjects in each arm will be recruited from three communities (Makerere University (*N* = 50), Kamwokya slums (*N* = 50) and Naguru go-down slums (*N* = 50) in each treatment arm and invited to participate. Participants will be evaluated at baseline, 6 and 12 months after baseline assessment.

A longitudinal process evaluation of the delivery of TSP using mobile phones and SMHS using mixed methods will run alongside the trial to assess acceptability, feasibility, fidelity, barriers and facilitators and how intervention recipients respond to the different intervention components. Open-ended exit interviews with recruited trained lay counsellors and study participants will seek to understand stressors in their communities, their own psychosocial support needs, and their knowledge regarding mental health after training, satisfaction, barriers and facilitators of participation in TSP sessions. Attendance registers and training logs will be used to track indicators of feasibility.

The study protocol is registered in the Pan African Clinical Trials Registry. The reporting of the trial will be in accordance with the Standard Protocol Items: Recommendations for Interventional Trials (SPIRIT) guidelines (39) for intervention trials (see Supplementary File S1) and the CONSORT statements for pilot randomized trials (40). The study was submitted to and approved by both the Makerere University College of Health Sciences Research Ethics Committee and the Uganda National Council of Science and Technology. All study participants will be required to provide written informed consent. Participants will receive a financial incentive to compensate for their time and defray internet data costs (if any). Figure 1 summarizes the trial profile.

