### Adverse event management

During the recruitment phase, potential participants exhibiting suicidal thoughts will undergo an assessment to evaluate their risk of suicide. Individuals diagnosed with depression who are identified as having a high risk of suicide will not be eligible for the study. Participants showing low to moderate suicide risk levels will be accepted into the study and will have their suicidal ideation evaluated at each counseling session. Should suicidal ideation persist after four counseling sessions, these participants will be directed to receive suitable care at the mental health departments of the hospitals involved in the study.

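### The adverse event definition is tied to TSP participation and AE interviews are timed post-intervention, which conflicts with monitoring of both arms and with the from-baseline schedule

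*Protocol article*

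**What the plan says.** Four statements in the protocol article bear on this point.

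- **Who is monitored, and when** (Participant safety): "Independent evaluators will monitor all participants for any adverse events at both 6- and 12-months post-intervention through a structured interview and report form".
- **What counts as an adverse event** (same section, next sentence): "any undesired or unintended sign, symptom, or medical occurrence linked to participation in tele-support psychotherapy". With its qualifier, the condition reads "linked to participation in tele-support psychotherapy, irrespective of its direct association with the therapy". Seriousness is built on that term: "Serious adverse events (SAEs) include any AE leading to outcomes such as death, a life-endangering situation", followed by admission and lasting disability. The one example offered is "suicide attempts resulting from an inadequate response to the tele-support psychotherapy sessions".
- **The trial's clock** (Study design): "Participants will be evaluated at baseline, 6 and 12 months after baseline assessment". Study measures and data collection schedule repeats this, with T1 at 6 months and T2 at 12 months after baseline.
- **Checks between visits** (Adverse event management): participants at low to moderate suicide risk "will have their suicidal ideation evaluated at each counseling session".

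Trial status reports 154 participants allocated to TSP plus SMHS and 146 to SMHS only.

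**The concern.** An SMHS-only participant does not take part in TSP. If an adverse event has to be linked to TSP participation, a suicide attempt, death or admission in that arm is neither an adverse event nor a serious one. The sentence on monitoring, however, sends evaluators to ask those same participants about adverse events. Whether a control-arm event is recorded as such would then depend on how each evaluator reads the text.

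The time anchor adds a second ambiguity. Counting from the end of the intervention gives dates different from T1 and T2, and gives no clear date at all for participants whose only care is SMHS.

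The trial enrols young people with depression, including some at low to moderate suicide risk, and is meant to supply data for designing a definitive trial. If the literal definition is used in coding, TSP shows events and the control arm shows none by construction, and no control rate for suicidal events is available.

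**Working it through.** There is no adverse event rate, safety margin or safety power in the article to reproduce. The check is mainly a comparison of texts.

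**1. Does the qualifier in the definition bring the control arm in?** The definition has two parts: a link to participation in TSP, and a statement that direct association with the therapy is not needed. The second part relaxes causality. It leaves the participation condition in place, and SMHS-only participants do not meet that condition. The two parts also sit badly together, since an event must be linked yet need not be associated.

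**2. Does the monitoring sentence bring the control arm in?** It covers all participants and any adverse events, so interviews are due in both arms. But the term it uses is the one then defined around TSP. Read by the monitoring sentence, a control-arm event is sought and recorded. Read by the definition, it does not qualify. Nothing in the text ranks one above the other.

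**3. Do serious events escape the problem?** No. They are described as adverse events with certain outcomes, so they inherit the participation condition.

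**4. How many participants are affected?** 154 + 146 = 300; 146 / 300 = 48.7%. This is the share of participants whose events lack a definition under the literal reading. It is not a count of lost events.

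**5. How far apart are the two clocks?** Let *L* be the time in months from baseline to the end of the intervention. Interviews at 6 and 12 months post-intervention fall at *L* + 6 and *L* + 12 months from baseline, so each is *L* months later than T1 or T2. For any *L* above zero, the second interview falls after the 12-month follow-up. The article gives eight TSP sessions but no interval between them, so *L* has to be assumed. Taking *L* as eight session intervals from baseline:

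| Assumed spacing | *L* (about) | First interview | Second interview |
|---|---|---|---|
| Two per week (4 weeks) | 1 month | month 7 | month 13 |
| Weekly (8 weeks) | 2 months | month 8 | month 14 |
| Every two weeks (16 weeks) | 4 months | month 10 | month 16 |

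For SMHS-only participants, *L* cannot be set. The Standard mental health services section describes unstructured counselling and/or medication management, with no course length or end. The Feasibility section does speak of eight sessions of either intervention, so the word intervention can cover both arms, but no end date for SMHS follows from that.

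**6. Is contact between visits equal?** TSP has eight study-run sessions. Controls were told to seek SMHS at a treatment centre. If every TSP participant were checked at every session and no control ever were, scheduled occasions would be 8 + 2 = 10 against 2. That is an upper bound only, for the reasons given under the objection.

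**The case against.** A reader might infer that control-arm harms simply do not count. The documents do not support that as fact. The monitoring sentence covers everyone, with independent evaluators and one structured form, and the definition can be read as a poorly worded rule that events during participation count whatever their cause. This stands to the extent that the text contradicts itself, rather than clearly excluding the control arm.

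A reader might also infer that no fair safety comparison is possible. That does not follow. Both arms are due the same interview, and an arm-neutral definition can be applied to what it collects. The article names no formal between-arm safety test, so there is no stated analysis that would be spoiled. The SAD PERSONS scale is also among the measures listed for the common questionnaire; it scores risk and does not record events, but it is not specific to one arm.

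The 10-against-2 contrast is not established. The session checks are described for participants at low to moderate suicide risk, sessions may be missed, SMHS includes counselling, and the checks are not said to feed adverse event counts. What stands is that session contact may differ by arm.

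Post-intervention may be a slip, since the other timing statements use the baseline clock. If so, the correction is one word, but it still has to be made.

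Finally, the article is condensed. The full protocol and the supplementary risk management plan are not shown and may hold clearer rules. The article cites that plan for suicide management rather than for the adverse event definition, and the definition it does print is the one at issue.

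**Conclusion.** The point holds as an internal contradiction with a practical consequence. The adverse event definition, the serious event definition and the only example are written around TSP, while monitoring covers both arms. Under the literal reading, events in 146 of 300 participants meet neither definition. The adverse event clock conflicts with the from-baseline schedule by the length of the intervention, and has no clear date in the SMHS-only arm.

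The 146 and the conflict of clocks come directly from the text. The month figures rest on assumed session spacing. No size can be given for lost events or for bias in rates, because the article states no event rate and does not say which definition evaluators used. The defect should be put right before any safety data are coded or reported; it does not make a safety summary unattainable.

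**What to change.** 1. Define an adverse event identically in both arms: any untoward occurrence from randomisation to T2, whatever its cause. Record judged relatedness to TSP or SMHS as a separate item. Let the serious event definition follow from this, and reword the example so that it is not specific to TSP.
2. Reconcile the time anchor so that adverse event interviews use the from-baseline clock (T1 and T2) in both arms.
3. Base any between-arm safety summary on those common interviews. List events detected only at counselling sessions separately, since session contact may differ by arm.
4. Recruitment ran from May to July 2023, so T2 for the last recruits would fall about July 2024 (July 2023 + 12 months), before the article appeared in February 2025. Prospective collection may therefore be over. Apply the arm-neutral definition when coding and reporting the interview data already collected, and state which definition the evaluators used and when the interviews actually took place.

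The cost is protocol and form wording plus some recoding, with slightly more control-arm events to record. No extra visits are needed. What cannot be recovered is any control-arm event that evaluators left unrecorded because they applied the literal definition; if that happened, it should be reported as a limitation.

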### Adverse event management

During the recruitment phase, potential participants exhibiting suicidal thoughts will undergo an assessment to evaluate their risk of suicide. Individuals diagnosed with depression who are identified as having a high risk of suicide will not be eligible for the study. Participants showing low to moderate suicide risk levels will be accepted into the study and will have their suicidal ideation evaluated at each counseling session. Should suicidal ideation persist after four counseling sessions, these participants will be directed to receive suitable care at the mental health departments of the hospitals involved in the study.

### Retention

To enhance adherence to the intervention sessions and maintain participant retention, lay health workers (LHWs) conducting the TSP sessions will receive a financial reward for their dedication to the project. Additionally, to re-engage participants who miss their TSP sessions, LHWs will be provided with airtime allowances to facilitate direct follow-up calls.

### Statistical analyses

The process evaluation of this pilot trial will adopt a mixed methods approach to thoroughly assess its primary outcomes, which include feasibility, acceptability, fidelity, the mediating processes behind observed effects, and the contextual factors acting as barriers or facilitators. For qualitative insights, accuracy checks will be performed on transcripts from Focus Group Discussions (FGDs) and Key Informant (KI) interviews, followed by translation into English and transcription. To ensure confidentiality, all interview data and notes will be anonymized and securely stored in the project's cloud-based folders. The qualitative data analysis will be conducted using MAXQDA Analytics Pro 2022 (Release 22.5.0), employing a grounded inductive approach to unearth recurring patterns and themes within the data. To enhance the analysis’ credibility, the thematic analysis will be collaboratively undertaken by at least three research team members. This collective effort aims to facilitate rich discussions, leading to a consensus on the emerging coding themes and a deeper understanding of the findings.

The interview data will initially be coded according to some themes corresponding to the focus questions. The codes will be used to construct matrix displays based on the co-occurrence of codes and the two treatment groups. The resulting matrix display will provide both the frequency and detailed content of responses, allowing us to assess how often responses varied between the two treatment groups. Inter-coder reliability will be assessed.

For the quantitative data, we will do bivariate analyses with *χ*^2^ tests and independent two-sample t tests to compare baseline demographic and psychosocial variables between study groups. Similarly, we will also do bivariate analyses to compare these variables between those who had completed all sessions (completers) and those who had not (non-completers).

We will assess randomization across the two arms by comparing socio-demographic characteristics and other potential confounding variables using chi-square for categorical variables and t-tests or other equivalent nonparametric tests, as appropriate, for continuous variables. Secondary outcomes will be the difference in follow-up mean depression, anxiety, stigma and social support scores between TSP-SMHS and SMHS (Control group) participants. These outcomes will be analyzed by ITT using generalized structural equation modelling. The STATA 16 statistical software will be used to conduct all analyses. Missing values will be imputed with multiple imputations.

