### Randomization and masking

A biostatistician will randomly assign participants to either an intervention or control group using specialized statistical software, ensuring impartiality as the biostatistician has no direct contact with participants. Randomized blocks of varying sizes will be used to enhance the balance between study arms and reducing sequence predictability. Participants, each assigned a unique study code for anonymity, will be identified only by their phone number and study code to the research team. This randomization will be applied across three distinct communities—Naguru, Kamyokya, and Makerere University—with 100 participants from each being randomized, ensuring the study's findings can be generalized across different population subsets. Although participants will know if they are receiving the experimental or control intervention, the nature of these interventions will be masked from independent outcome assessors and data analysts to prevent assessment bias and ensure objective outcome evaluation.

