### Study measures and data collection schedule

Study participants in the intervention and control arms will be asked to complete an interviewer-administered face-to-face or telephone-based standardized questionnaire to collect data on primary and secondary outcomes at baseline (T0), 6 months (T1), and 12 months (T2) after baseline.

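### The secondary effects are printed as differences in follow-up means, with neither the baseline score nor community named, which costs precision if fitted that way; separately, the planned baseline tests between arms cannot assess randomisation.

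*Protocol article*

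**What the plan says.** All references are to the protocol article.

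- **Effect measure** (Statistical analyses): "Secondary outcomes will be the difference in follow-up mean depression, anxiety, stigma and social support scores between TSP-SMHS and SMHS".
- **Model** (same section, next sentence): "These outcomes will be analyzed by ITT using generalized structural equation modelling". Missing values are to be multiply imputed. No covariates are listed or ruled out.
- **Baseline data** (Study measures and data collection schedule): a questionnaire is to be used "to collect data on primary and secondary outcomes at baseline (T0), 6 months (T1), and 12 months (T2) after baseline". The depression, anxiety, stigma and social support scores should therefore all exist at T0.
- **Community** (Randomization and masking): "This randomization will be applied across three distinct communities", "with 100 participants from each being randomized". Study design plans 50 per arm in each community. This reads as allocation within community, although the article does not use the word stratified.
- **Baseline tests** (Statistical analyses): "We will assess randomization across the two arms by comparing socio-demographic characteristics and other potential confounding variables using chi-square for categorical variables", with t-tests or nonparametric equivalents for continuous variables. An earlier paragraph of that section already plans chi-square tests and "independent two-sample t tests to compare baseline demographic and psychosocial variables between study groups".

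**The concern.** A participant's score six or twelve months later usually depends in part on the score at entry. A model without the entry score leaves that part in the error term, so the standard error is larger than the data require. The same applies to community if outcomes differ between two slum areas and a university. In addition, when allocation is balanced within community, a standard error that ignores community overstates the sampling variability of the arm difference.

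This matters beyond the pilot's own intervals. Sample size estimation justifies 300 participants partly by the value of a precise variance estimate for the main trial. Which variance is carried forward, unadjusted or residual, bears directly on that trial's size.

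The baseline tests are a separate matter. If allocation was properly random, any difference between arms at baseline arose by chance and the null hypothesis is true by design. A small p-value then says nothing about whether randomisation worked, and a large one does not confirm it.

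**Working it through.** **Plan's own figures.** The article states no alpha, power, effect size, SD or baseline correlation, so there is no power calculation to reproduce. The allocation counts agree: 3 × 50 = 150 per arm, 3 × 100 = 300, and 154 + 146 = 300 actually randomised (Trial status).

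**1. Unadjusted precision.** In SD units and with no loss to follow-up, SE = √(1/154 + 1/146) = 0.1155. The 95% half-width is 1.96 × 0.1155 = 0.226 SD. With 150 per arm it is also 0.226. With an assumed 20% attrition, the SE is 0.129 and the half-width 0.253.

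**2. Adjusting for the T0 score.** The variance is multiplied by 1 − r² and the SE by √(1 − r²). Here r is the correlation between T0 and follow-up scores, which is assumed because the article gives none.

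| r (assumed) | Variance saved, r² | SE ratio | 300 worth, 300/(1 − r²) | Half-width (SD) |
|---|---|---|---|---|
| 0.2 | 4% | 0.980 | about 312 | 0.222 |
| 0.3 | 9% | 0.954 | 330 | 0.216 |
| 0.5 | 25% | 0.866 | 400 | 0.196 |
| 0.6 | 36% | 0.800 | 469 | 0.181 |

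**3. Main-trial size.** If the main trial is analysed with baseline adjustment but sized on the unadjusted SD, it is larger than needed by a factor of 1/(1 − r²). This is 1.04, 1.10, 1.33 and 1.56 for the four values of r.

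**4. Community.** If community explains a share R² of outcome variance (assumed), adjusting for it multiplies the SE by √(1 − R²). For R² of 1%, 5% and 10%, the SE falls by 0.5%, 2.5% and 5.1%. These savings do not simply add to those in step 2, because the baseline score may already carry part of the community difference.

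With exact balance within community, a nominal 5% test that ignores community has type I error of about 2 × [1 − Φ(1.96/√(1 − R²))]:

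- R² = 5%: 1.96/0.975 = 2.01, giving 0.044
- R² = 10%: 1.96/0.949 = 2.07, giving 0.039
- R² = 20%: 1.96/0.894 = 2.19, giving 0.028

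A simulation of 20,000 runs with 50 per arm per community gave similar values: 0.043, 0.041 and 0.029. The test errs on the cautious side; it is not invalid.

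**5. Baseline tests.** The article lists six socio-demographic variables: age, gender, children, education, relationship and employment. It also lists nine psychosocial or clinical ones: depression symptoms, suicide risk, major depression, anxiety, alcohol, self-esteem, disability days, social support and stigma. That makes about 15. At an assumed 5% level, 15 × 0.05 = 0.75 differences with p<0.05 are expected under perfect randomisation. If the tests are independent, the chance of at least one is 1 − 0.95¹⁵ = 0.54; with 10 tests it is 1 − 0.95¹⁰ = 0.40.

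**The case against.** The strongest objection is that the article does not say the analysis is unadjusted. A difference in follow-up means is also what a baseline-adjusted model estimates, and the model named in the next sentence can include both covariates. The abstract speaks of changes in depressive symptoms, so the authors may well have the T0 score in mind. A covariate list is often left to an analysis plan, which is not shown here. This stands: a reader might infer that baseline and community are deliberately excluded, but the text only fails to name them. The loss of precision is therefore conditional on fitting the definition as printed.

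A reader might also infer that the baseline tests take the place of adjustment, or that their p-values will choose the covariates. The documents say neither. The variables are called potential confounders, but no selection step is described.

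The size of the loss is also open. Entry is limited to mild to moderate depression and follow-up is at 6 and 12 months. Both could lower r for the depression score, and at r = 0.2 the saving is only 4% of variance. The number of baseline tests and their level are assumed as well.

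Finally, the stakes are modest. The primary outcomes are feasibility and acceptability, and the article says the pilot does not aim to prove superiority.

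These points reduce the claim without removing it. Naming a collected baseline score and the randomisation groups in the effect definition is a specific gain at almost no cost. The stated purpose of the baseline tests is explicit, and no analysis plan could make them serve it.

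**Conclusion.** The point holds in two parts of different certainty.

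- **Baseline tests (high certainty).** The stated purpose is explicit and cannot be met. No decision is attached to the results, so no estimate is shown to be affected. The 54% figure rests on 15 independent tests at 5%.
- **Effect definition (conditional).** Fitted as printed, without the T0 score or community, the model gives wider intervals than the same data allow. The variance saved by adjusting for baseline runs from 4% to 36% over assumed r from 0.2 to 0.6. The further gain from community is small (SE down 0.5% to 5.1% for an assumed 1% to 10% of variance), and ignoring it makes the test mildly conservative.

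The consequence is lost precision and less efficient planning estimates for secondary outcomes of a pilot. Bias is not at issue: with proper randomisation, chance baseline differences average to zero over repetitions.

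**What to change.** 1. In the analysis text, define each secondary effect as the between-arm mean difference at T1 and at T2, adjusted for the same score at T0 and for community (two indicator variables). Fit both time points within the planned structural equation model, and carry the same variables in the imputation model.
2. Fix these covariates in writing before the analysts are unmasked.
3. Report the residual SD and the baseline/follow-up correlation for each score, beside the unadjusted SD, so that the main trial can be sized for the analysis it will use.
4. State plainly whether allocation was stratified by community.
5. Present baseline characteristics by arm descriptively and delete the between-arm significance tests. Any check on randomisation should rest on the allocation procedure and its records.

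The cost is a change of wording and three model terms per outcome. No new measurements are needed, since T0 scores and community are already part of data collection. Trial status reports that baseline analysis is underway, so the change to the baseline table is best made now.
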